**Fig. 1 Fig1:**
[figure not shown]
Study flow chart. Eligible participants with coronary heart disease (CHD) after percutaneous coronary intervention (PCI) will be randomly allocated to the intervention or control group. The exercise intervention is an outpatient clinical rehabilitation program with targeted intensity, which includes a 30-min session three times a week for 8 weeks. Participants in the control group will be prescribed the same number of exercise sessions without targeted intensity. Cardiopulmonary exercise testing will be performed before and after the 8-week cardiac rehabilitation program to assess changes in cardiopulmonary function

**Table 3 Tab3:** A stratified randomization scheme based on gender

Male			Female		
Serial number	Random number	Group	Serial number	Random number	Group
1	0.699718	A	1	0.299478	A
2	0.474505	B	2	0.228082	A
3	0.278238	A	3	0.905825	B
4	0.063581	B	4	0.288985	B
5	0.543526	A	5	0.204267	B
6	0.645542	A	6	0.004536	A
7	0.606382	A	7	0.876704	A
8	0.358782	A	8	0.765598	A
9	0.913533	B	9	0.989875	B
10	0.394207	B	10	0.735247	B
11	0.101518	A	11	0.968638	A
12	0.830019	B	12	0.975038	A
13	0.454501	B	13	0.355564	A
14	0.941391	B	14	0.730377	B
15	0.748873	B	15	0.087323	B
16	0.736089	B	16	0.318215	B
17	0.026114	A	17	0.794593	B
18	0.294124	A	18	0.322396	A
19	0.801002	A	19	0.180908	A
20	0.448855	B	20	0.552161	B

Microsoft Excel Rand is performed to generate random numbers between 0 and 1, last digit even number for group A (intervention) and odd for group B (control). Patients are then allocated to intervention and control groups chronologically

### Sample size determination

Given the pilot nature of this trial, we will focus on the feasibility of the study and ensure that the exercise intervention runs smoothly, we will not calculate a sample size to determine the power in this study [20]. However, it is recommended that a minimum of 30 participants is required to achieve sufficient precision to enable sample size calculation for subsequent studies [21]. Therefore, we plan to recruit 40 participants, which will allow the completion of data collection from 30 subjects, with a 75% participant retention rate.

### Study procedures

#### Telephone follow up before exercise intervention

Eligible patients who are willing to participate in our CR program will be contacted by a telephone call 1–2 weeks after PCI. Patients in a stable condition will be recommended to start outpatient rehabilitation in our clinic as soon as possible. A “stable condition” is determined by the following: the participant self-reports satisfaction over the phone and denies recent chest pain or any other disorders that need additional medications; the physician confirms that the patient’s vital signs are stable and within normal limits at the outpatient clinic, for example, resting heart rate < 100/min, resting systolic blood pressure < 140 mmHg and diastolic blood pressure <90 mmHg. If an individual is not considered stable, there is an additional waiting period of 2 weeks. That person will be checked again 2 weeks later to determine if he/she is sufficiently stable to participate in the CR program.

#### Exercise prescription

All participants will undergo cardiopulmonary exercise testing (CPET) to obtain initial parameters of anaerobic threshold (AnT), which is defined as the highest sustained intensity of exercise for which measurement of oxygen uptake by means of CPET can account for the entire energy requirement, on the first day of the CR program. The targeted intensity is determined based on the heart rate recorded 1 min before AnT during CPET to provide an individualized CR training prescription for each participant in the intervention group. Thus, exercise intensity will not be affected by medications because the intensity is determined on an individual basis. Participants in the control group will undergo the same number of exercise sessions without targeted intensity. The CR program also includes CHD management strategies such as concomitant therapy, balanced diet nutrition, psychosocial consultation, and smoking cessation. There are no differences in disease management between the two groups.

#### Exercise intervention

The exercise intervention is an outpatient clinical rehabilitation program delivered one-on-one to individuals in a 30-min session and three times a week for 8 weeks in the hospital outpatient clinic. The 30-min CR procedure includes 5 min of warm-up exercise, 20 min of cycle ergometer (Ergoline GmbH, Germany) exercise with targeted intensity, and 5 min of cool-down exercise. The targeted intensity is set as the heart rate 1 min before AnT based on CPET. We expect that exercise parameters will improve gradually as individuals reach their targeted intensity more frequently with time over the 8 weeks. Participants are closely monitored using a heart rate monitoring device connected to the cycle ergometer and will be guided by the CR team, which consists of cardiologists, rehabilitation physicians, physiotherapists, nurses, and clinical research coordinators. The research coordinator will record the attendance of each participant and will ask the participant to come on the weekend to compensate for any missed sessions. In addition, the CR protocol can be extended to accommodate an intervening illness. Nevertheless, the participant is allowed to quit the program at any time if he/she wants to do so. Participants will be followed closely to ensure adherence. All CR providers are trained to follow the same protocol to ensure intervention fidelity. Participants in the control arm will receive telephone calls once a week to monitor their physical conditions and will be encouraged to take a walk at least 30 min at a time and three times a week during the 8-week study at home but not at the program center. The information for the control group will be recorded using activity tracking apps such as activity tracker bands, watches and smartphones so that the authors will know how active the control-arm participants are. The second CPET will be conducted after the 8-week CR program. Graduates will also be advised to take concomitant medications, continue engaging in appropriate exercise, eat a balanced diet, and quit smoking.

#### Telephone follow up after 3 months

Participants in both groups will receive follow-up calls 3 months after the end of the program to provide information on their most updated health condition such as smoking status, cardiac risk control medication (aspirin, statins, beta-blockers, etc.), diet, psychological status, and physical activity. At the end of the CR session, patients in both the intervention and control groups will be prescribed a home exercise program using community-based rehabilitation facilities and will be encouraged to live a more active lifestyle.

### Data collection

Assessors are trained to collect trial data from the outpatient clinic and laboratory. The following data will be collected from all participants before and after the rehabilitation training as shown in the SPIRIT diagram (Fig. 2): the aerobic metabolism parameter (AnT), clinical indicators (blood pressure, heart rate, body mass index, smoking status, and comorbidities), laboratory indicators (total cholesterol, high-density lipids (HDL)-cholesterol, low-density lipids (LDL)-cholesterol, triacylglycerides, apolipoproteins, homocysteine, glucose, etc.), and blood samples for additional biomarkers (C-reactive protein, macrophage inflammatory protein-1α, pentraxin-3, monocyte chemotactic protein-1, interleukins, transforming growth factor-β, interferon-γ, brain natriuretic peptide, growth differentiation factor-15, vascular endothelial growth factor-B, myeloperoxidase, adiponectin, matrix metalloproteinase-1, 2, or 9, matrix metalloproteinases tissue inhibitor-1, phosphodiesterase-9A). Data will be collected at 3 months to assess the short-term prognosis and risk factors for cardiac adverse events after the CR program.

**Fig. 2 Fig2:**
[figure not shown]
Standard Protocol Items: Recommendations for Interventional Trials (SPIRIT) timeline of measurements. Recommended content for the schedule of enrollment, intervention, and assessments. ELISA, enzyme linked immunosorbent assay; PCI, percutaneous coronary intervention

### Outcome measurements

The primary outcome is the feasibility of the trial. Recruitment rate and retention rate as feasibility parameters will be analyzed. The secondary outcomes are aerobic metabolism parameters and clinical and laboratory indicators that will be used to identify cardiac risk factors such as hypertension, dyslipidemia, diabetes mellitus, obesity, and smoking status. The exploratory outcomes are additional biomarkers such as inflammatory markers (C-reactive protein, macrophage inflammatory protein-1α, pentraxin-3, monocyte chemotactic protein-1, interleukins, transforming growth factor β), an immune-modulatory marker (interferon-γ), myocyte stress markers (brain natriuretic peptide and growth differentiation factor-15), a left ventricular dysfunction marker (vascular endothelial growth factor-B), an oxidative stress marker (myeloperoxidase), a metabolic hormone (adiponectin), extracellular-matrix remodeling markers (matrix metalloproteinase-1, 2, 9, and matrix metalloproteinases tissue inhibitor-1), and a signal transduction regulator (phosphodiesterase-9A) to further evaluate a patient’s underlying cardiovascular function at the molecular level.

### Data assessment

The objective of this pilot study is to test the feasibility of recruitment, retention, intervention, and collection of data on aerobic metabolism parameters and clinical and laboratory measurements at the same time. Mean changes in outcomes over time will be summarized graphically and descriptively within each group. These changes will be compared between groups and will be described with associated 95% confidence intervals to explore possible effects of the intervention, recognizing that this pilot trial is not powered to detect clinically meaningful effects. Feasibility parameters, such as recruitment rate and retention rate, will be analyzed to determine whether it is worth continuing to conduct a large-scale trial that builds from the current pilot trial. The key feasibility criteria include recruitment of 40 participants, attainment of a 75% participant retention rate, and measurement of all outcomes in 90% of all participants. These parameters will be assessed at the end of the pilot trial by a statistician who is not involved in the study.

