However, this pilot trial has several limitations. Given the large age range of subjects from 45 to 80 years and the relatively small sample size after allocation to subgroups (male and female), physiology and biomarker profiles can vary greatly. The second limitation is the disparate modes between the intervention (cycle ergometer) and control (walk) groups. Specifically, the intervention group receives cycle ergometer training for exercise safety and to prevent patients from falling during treadmill training whereas the control arm does not receive this training. Moreover, whereas all of the intervention participants will be monitored with a standardized heart rate monitor during each intervention session, activity in the control arm will not be monitored using the same tool and will instead be monitored by whatever tracking app the participant has available. As a consequence, the data quality may be of very low quality or missing in the control arm. The third limitation is that outcome assessment of metabolism and clinical indicators (blood pressure, heart rate etc.) is not blinded. As a consequence, the quantitative results of the trial may not be completely reliable as there could be different quality of assessments in the two groups of the trial. However, a statistician who is not involved in the study will be invited to assess the data according to a pre-specified analysis plan, and the groups will be labeled A and B, to ensure that the data are analyzed blind. In a future larger trial, procedures will be put in place to ensure blinding of outcome assessors to avoid bias. The feasibility measures are the focus of the current pilot study and these will not be subject to potential observer bias.

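### Feasibility of the exercise intervention is a stated objective, but no listed success criterion measures whether the exercise was delivered

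*Protocol article*

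**What the plan says.** All references are to the protocol article.

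- **Objective (Data assessment):** "The objective of this pilot study is to test the feasibility of recruitment, retention, intervention, and collection of data". Sample size determination also names the smooth running of the exercise as a focus of the pilot.
- **Primary outcome (Outcome measurements):** feasibility, with the sentence "Recruitment rate and retention rate as feasibility parameters will be analyzed".
- **Success criteria (Data assessment):** "The key feasibility criteria include recruitment of 40 participants, attainment of a 75% participant retention rate". A third criterion, on completeness of the data, is worded as "measurement of all outcomes in 90% of all participants". The same section says that the feasibility parameters will decide whether a large trial is worth pursuing.
- **Planned completers (Sample size determination):** "we plan to recruit 40 participants, which will allow the completion of data collection from 30 subjects, with a 75% participant retention rate".
- **Delivery data (Exercise intervention):** "The research coordinator will record the attendance of each participant". Missed sessions are made up at weekends, and heart rate is monitored on the ergometer against an individual target. The programme is three sessions a week for 8 weeks. The control arm walks at home.

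**The concern.** The objective has four parts: recruitment, retention, intervention and data collection. Recruitment, retention and data collection each have a numeric threshold. Intervention has none, and the primary outcome names only recruitment and retention rates. The data that would show whether the exercise took place are collected but feed no criterion.

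The retention criterion gives a single rate with no arm named, and the two arms carry very different burdens: supervised hospital sessions in one, walking at home in the other. Good retention in control can offset poor retention in the arm whose feasibility is in question.

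At stake is the decision that the pilot exists to inform. A favourable answer on the listed criteria would not show that the exercise programme can be delivered to these patients.

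**Working it through.** **1. The plan's own figure.** 30 completers at 75% retention need 30 / 0.75 = 40 recruited, and 40 × 0.75 = 30. This reproduces.

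**2. Objectives against criteria.**

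| Part of the objective | Criterion |
|---|---|
| Recruitment | 40 participants |
| Retention | 75% |
| Data collection | all outcomes in 90% |
| Intervention | none listed |

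**3. Can the criteria be met without delivery?** Sessions prescribed: 3 × 8 = 24 per person, so 20 × 24 = 480 in the exercise arm. Suppose every exercise participant attends one session and all 40 participants return for the second exercise test and blood sample. Delivery is 20/480 = 4%. Recruitment is 40, retention 40/40 and completeness 40/40, so every listed criterion is met. This holds whichever denominator the 90% uses. It assumes that retained means still in the study for the final measurements. The article does not define the term, but Sample size determination ties the 75% to completed data collection.

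**4. Retention without an arm.** With the target of 20 per arm, 75% needs 30 retained. 10/20 + 20/20 = 30/40 meets it. The table gives exact binomial chances, with the true retention rates assumed because the article gives none by arm.

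| True retention, exercise / control | P(at least 30/40) | P(at least 15/20 in exercise arm) |
|---|---|---|
| 50% / 95% | 42% | 2% |
| 55% / 95% | 59% | 6% |
| 60% / 95% | 74% | 13% |

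These figures concern the retention criterion alone.

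**5. Adding the 90% criterion.**

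- *Literal, all participants:* 0.90 × 40 = 36. If those lost are not measured, 10/20 + 20/20 gives 30/40 = 75% and fails. At most 4 can be unmeasured, so at least 16/20 = 80% of the exercise arm must be measured. At 55% / 95%, P(at least 36/40) = 0.9%.
- *Among retained:* 0.90 × 30 = 27. The 10/20 + 20/20 case can then pass everything.

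The literal reading does not fit the rest of the plan. The 30 planned completers could never reach 36, and a 75% retention criterion would be redundant beside it. With true retention of 75% in both arms, P(at least 36/40) = 1.6%.

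**6. Cost of a hard rule in one arm.** At a true exercise-arm retention of 75%, P(at least 15/20) = 62%, so the rule fails 38% of the time. An observed 15/20 has an exact 95% interval of 51% to 91%, and 10/20 one of 27% to 73%.

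**The case against.** The list of criteria is introduced as what the key criteria include, so it is not closed. Attendance is recorded and adherence followed closely, so whoever weighs the large trial will have those data. The article also refers to a prespecified analysis plan, which is not shown, and commits to CONSORT reporting. Retention by arm and a definition of retained could well sit there.

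Much of this stands for the reporting of retention: the article does not say that retention will be reported only overall. It does not remove the main point. The article itself fixes numeric thresholds for three of its four feasibility aims and gives none for the fourth anywhere in its text.

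A reader might infer that the pilot can be declared feasible with half the exercise arm lost, and cite the 59% as the chance of a false go. The document does not support that without a condition. The literal 90% criterion blocks that case if lost participants are unmeasured. It passes only if the 90% is taken among retained participants, or if those lost are still measured.

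A reader might also want to redesign the control arm's activity measurement, since control activity "will instead be monitored by whatever tracking app the participant has available" while "Participants in the control arm will receive telephone calls once a week to monitor their physical conditions". The Discussion already discloses this as a limitation. Self-report by telephone has its own recall problems, and the choice does not bear on the missing criterion.

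**Conclusion.** The concern holds for exercise delivery. The listed criteria can all be met with about 4% of the prescribed sessions attended, under either reading of the 90%. The only assumption is that a participant who returns for the final measurements counts as retained.

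It holds with a condition for retention. The 75% criterion alone is met with 10/20 in the exercise arm, but the full set is met in that case only if the 90% is taken among retained participants or those lost are still measured. The chances by arm rest on assumed retention rates and on the 20/20 target split, which the randomisation by last digit does not force. The denominator of the 90% criterion is itself unclear, and its literal reading conflicts with the planned 30 completers.

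This should be corrected, since the criteria steer the decision on a large trial and the data needed are already being collected.

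**What to change.** 1. Add a prespecified delivery criterion based on the attendance already recorded: the share of exercise-arm participants who attend at least a stated number of the 24 sessions. The sponsor sets both figures before the end-of-trial assessment.
2. Report the share of sessions in which the target heart rate was reached.
3. Define retained, report retention by arm, and weigh exercise-arm retention with its confidence interval in the decision.
4. State the denominator of the 90% criterion so that it agrees with 75% retention.

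**Cost.** This is protocol wording and a tabulation of existing records. The hurdle becomes harder to pass, and noticeably so if a hard 15/20 rule is set in one arm (38% failure at a true 75%). That is why item 3 asks for the interval to be weighed and sets no cut-off. The Trial status section reports 13 participants already enrolled, so the criterion would be added during the trial. Its date should be recorded, and the threshold set without looking at the attendance data so far.

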### Randomization

Participants will be randomly allocated (1:1 ratio) to either the intervention or control group once screening assessments are completed and eligibility for the study is confirmed (Fig. 1). A research coordinator will generate the random allocation sequence, enroll participants, and assign participants to interventions. A stratified randomization scheme based on gender will be used. Microsoft Excel Formula Rand will be used to allocate patients to the intervention or control group. A random number between 0 and 1 will be generated for each patient; if the last digit is an even number the patient will be assigned to group A (intervention) and if the last digit is an odd number the patient will be assigned to group B (control) (Table 3). Forty participants will be allocated randomly to group A (intervention exercise group with targeted intensity, *n* = 20) or B (control group with leisure exercise, *n* = 20).

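### The between-group comparison is framed on mean changes with no stated baseline adjustment, which costs some precision and leaves part of any chance baseline difference in the estimate

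*Protocol article*

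**What the plan says.** The protocol article, Data assessment, sets out the handling of outcomes in two steps. First: "Mean changes in outcomes over time will be summarized graphically and descriptively within each group". Then: "These changes will be compared between groups and will be described with associated 95% confidence intervals". The stated purpose is "to explore possible effects of the intervention, recognizing that this pilot trial is not powered to detect clinically meaningful effects". No model, baseline covariate or gender term is named, and the text does not call the comparison unadjusted either.

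Other sections that bear on the point:

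- Randomization: "Participants will be randomly allocated (1:1 ratio) to either the intervention or control group", and "A stratified randomization scheme based on gender will be used".
- Sample size determination: "we will not calculate a sample size to determine the power in this study", but "we plan to recruit 40 participants, which will allow the completion of data collection from 30 subjects, with a 75% participant retention rate". The figure of 30 is justified there by the precision needed to size later studies.
- Data collection: the outcomes are measured before and after training, so a baseline value is available for each.
- Outcome measurements: "The primary outcome is the feasibility of the trial".
- Discussion, limitations: the data will be analysed under a pre-specified analysis plan. That plan is not shown.

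**The concern.** A difference in mean change removes the baseline value one for one. When follow-up and baseline have equal SDs and correlation r, the efficient amount to remove is r times the baseline difference. Removing all of it over-corrects by (1 − r). This has two consequences. The interval is wider than it needs to be, and an arm that happens to start high tends to show a larger fall through regression to the mean.

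Both effects matter more in small samples, where chance baseline differences are larger. The Discussion itself notes the wide age range, the small numbers by gender and the resulting variability in physiology and biomarkers.

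What is at stake is the precision of the exploratory effect estimates, and the SD carried into planning the next trial. The decision on feasibility is not at stake.

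**Working it through.** **The plan's own figure.** 30 completers / (1 − 0.25) = 40 recruited, which matches the stated target.

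**Inputs.** From the document: 1:1 allocation, 40 recruited, 30 completers, 95% intervals. Assumed: completers split evenly (n = 15 per arm, N = 30), equal SDs at both times, and r from 0.3 to 0.9. All widths are in units of the outcome SD.

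**Formulas for the expected 95% half-width.**

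- Change score: t(N − 2) × √[2(1 − r) × 2/n]
- Baseline-adjusted: t(N − 3) × √[(1 − r²) × (2/n) × (1 + 1/(N − 4))]
- Baseline plus a gender term that predicts nothing: t(N − 4) × √[(1 − r²) × (2/n) × (1 + 2/(N − 5))]

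The last factor in the second and third formulas is the small-sample price of estimating the covariate coefficients.

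**Worked case, n = 15, r = 0.5.**

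- Change: 2.048 × √(1.0 × 0.1333) = 0.748.
- Adjusted: 2.052 × √(0.75 × 0.1333 × 1.0385) = 0.661.
- Ratio: 0.661 / 0.748 = 0.88, so about 12% narrower.

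**Range, n = 15 per arm.**

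| r | change | adjusted | ratio | ratio with non-prognostic gender |
|---|---|---|---|---|
| 0.3 | 0.885 | 0.728 | 0.82 | 0.84 |
| 0.5 | 0.748 | 0.661 | 0.88 | 0.90 |
| 0.7 | 0.579 | 0.545 | 0.94 | 0.96 |
| 0.8 | 0.473 | 0.458 | 0.97 | 0.99 |
| 0.9 | 0.335 | 0.333 | 0.995 | 1.02 |

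With all 20 per arm the baseline-adjusted ratios are close to these: 0.82, 0.88, 0.94 and 0.99 at r = 0.3, 0.5, 0.7 and 0.9.

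A simulation of 4,000 trials per setting at 15 per arm gave mean width ratios of 0.883 (r = 0.5) and 0.941 (r = 0.7), in agreement. The gain is an average: the adjusted interval was the narrower one in 90.5% of simulated trials at r = 0.5 and 76% at r = 0.7.

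The variance of a change is 2(1 − r), which exceeds 1 when r is below 0.5. There the change score is less precise than comparing follow-up values with no use of baseline: at r = 0.3, 0.885 against 2.048 × √(2/15) = 0.748.

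**Chance baseline difference.** Its standard error is √(2/15) = 0.365 SD. A difference of one standard error moves the change contrast by (1 − r) × 0.365 in the opposite direction: 0.18 SD at r = 0.5, 0.11 at r = 0.7 and 0.04 at r = 0.9. This holds conditionally on the imbalance. Averaged over randomization, the shift is zero.

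**Gender.** Table 3 gives 10 A and 10 B in each gender, but only when each list of 20 is used up. The first 8 male lines are 6 A and 2 B. How strongly gender predicts the outcomes is not given, so no precision gain from a gender term can be calculated.

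**The case against.** The strongest reply is that the text does not state an unadjusted analysis. A change can be regressed on arm, baseline and gender, and the arm estimate and interval are then identical to those from modelling the follow-up value on the same terms. The wording is compatible with that. The article is a condensed account and points to a separate analysis plan, where covariates are normally set. This stands. It means the point concerns how the comparison reads, not a demonstrated error, and it limits confidence.

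Two further replies also stand in part. The size depends on an r that the document does not give, and the benefit all but vanishes at high r. And because baseline and follow-up values are both collected, planners of the next trial can compute whichever SD or correlation they need, whatever contrast is reported. The loss for planning is therefore avoidable, provided the right SD is used.

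A reader might infer several stronger points that the documents do not support:

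- That baseline is ignored. It is subtracted in full; the fault is over-correction.
- That the gender strata are ignored. No gender term is stated, but none is ruled out.
- That the effect estimate is biased. Over randomization it is not.
- That skewed biomarkers invalidate the intervals. The document gives no distributions, so no log-scale recommendation is made here.

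**Conclusion.** The point holds as a low-severity improvement. The natural reading of Data assessment is a difference in mean change. Compared with baseline adjustment at about 15 completers per arm, that gives an interval wider by about 22% at r = 0.3 (0.885/0.728), 13% at r = 0.5 (0.748/0.661), 6% at r = 0.7 (0.579/0.545) and under 1% at r = 0.9 (0.335/0.333). It also leaves (1 − r) of any chance baseline difference in the estimate, with the sign reversed.

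The conclusion rests on equal SDs before and after, an even split of completers, an assumed r, and the absence of adjustment in the analysis plan that is not shown. The recruitment, retention and outcome-completeness criteria do not depend on this comparison. The planning of the next trial does, to a modest degree: in large samples, the change-score variance is 2/(1 + r) times the adjusted one, or 1.33 at r = 0.5 and 1.18 at r = 0.7. A trial sized on the change-score SD would be larger by that factor than a baseline-adjusted design needs.

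**What to change.** State in Data assessment that each between-group difference in a continuous outcome is estimated from a linear model of the post-programme value (or, equivalently, the change) on arm and baseline value. Include gender because it is the stratification factor. Report the 95% interval, and report the residual SD for planning the next trial. Keep the within-group mean changes as descriptive tables and graphs. If the analysis plan already specifies this, one sentence saying so is enough.

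The change is to wording only and needs no new data. With 30 completers, residual degrees of freedom fall from 28 to 27 with baseline, or to 26 with baseline and gender. If gender turns out not to be prognostic, the full model still gives a narrower interval than the change score at r = 0.5 (ratio 0.90) and r = 0.7 (0.96), and a slightly wider one at r = 0.9 (1.02). Trial status reports 13 patients enrolled with recruitment still open, so the wording can be settled before the final analysis.

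### For continuous outcomes the article states only a comparison of mean changes and names no baseline covariate; baseline adjustment would usually give narrower intervals from data already collected

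*Protocol article*

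**What the plan says.** The Data assessment section of the protocol article sets out the analysis of the non-feasibility outcomes in two steps. Within groups, "Mean changes in outcomes over time will be summarized graphically and descriptively within each group". Between groups, "These changes will be compared between groups and will be described with associated 95% confidence intervals". The section presents this as exploration, "recognizing that this pilot trial is not powered to detect clinically meaningful effects". It names no model, test or covariate.

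The Data collection section confirms that baselines exist: "The following data will be collected from all participants before and after the rehabilitation training". The list that follows covers anaerobic threshold, clinical indicators, laboratory indicators and the additional biomarkers.

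On numbers, the Sample size determination section says "we plan to recruit 40 participants, which will allow the completion of data collection from 30 subjects, with a 75% participant retention rate". The Randomization section gives 20 per arm, stratified by gender. The Discussion refers to a pre-specified analysis plan, which is not shown.

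**The concern.** A comparison of mean changes subtracts the whole baseline value, which fixes the slope of the follow-up value on baseline at 1. With equal SDs before and after, the actual slope is the before-after correlation rho, which is below 1. The change score then corrects too much for baseline. This adds noise, and part of any chance baseline difference between the arms passes into the estimated effect with reversed sign (regression to the mean).

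What is at stake is precision in a small trial. The sample size rationale refers to having enough precision to plan later studies, and there may be only about 15 completers per arm. The SD carried into that planning also depends on the method: the SD of change is larger than the residual SD after baseline adjustment unless rho is close to 1.

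**Working it through.** **Inputs.** From the article: 40 randomised 1:1 and 75% retention. Assumed: completers split equally between arms; equal SDs before and after (set to 1, so results are in SD units); within-arm before-after correlation rho, which the document does not give and is therefore shown as a range.

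**The article's own figure.** 30 / 0.75 = 40, so the recruitment target reproduces. The retention floor leaves 15 per arm.

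**Interval half-widths, n = 15 per arm.**

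- Mean change: t(28) × sqrt(2(1 - rho)) × sqrt(2/n), with t(28) = 2.048 and sqrt(2/15) = 0.365.
- Baseline-adjusted: t(27) × sqrt(1 - rho²) × sqrt(2/n) × sqrt(1 + 1/(2n - 4)), with t(27) = 2.052. The last factor, sqrt(1 + 1/26) = 1.019, is the price of estimating the slope.

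At rho = 0.5:

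- mean change: 2.048 × 1.000 × 0.365 = 0.748
- adjusted: 2.052 × 0.866 × 0.365 × 1.019 = 0.661
- ratio: 0.748 / 0.661 = 1.13

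| rho | mean change | baseline-adjusted | mean change relative to adjusted |
|---|---|---|---|
| 0.3 | 0.885 | 0.728 | 22% wider |
| 0.5 | 0.748 | 0.661 | 13% wider |
| 0.7 | 0.579 | 0.545 | 6% wider |
| 0.8 | 0.473 | 0.458 | 3% wider |
| 0.9 | 0.335 | 0.333 | 0.5% wider |
| 0.95 | 0.237 | 0.238 | 0.8% narrower |

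A simulation with 6,000 trials per value of rho (0.8 was not simulated) gave width ratios of 1.216, 1.131, 1.064, 1.005 and 0.992, in agreement. With all 20 per arm the ratios for the six rows are 1.22, 1.14, 1.07, 1.04, 1.01 and 1.00.

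**Chance imbalance.** The baseline difference D between arms has standard error sqrt(2/15) = 0.365 SD at 15 per arm and sqrt(2/20) = 0.316 SD at 20. The probability that it exceeds 0.5 SD in either direction is 0.171 at 15 per arm (0.5/0.365 = 1.37) and 0.114 at 20 (0.5/0.316 = 1.58).

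Given D, the difference in mean change shifts by -(1 - rho)D. For D = 0.5 SD the size of the shift is 0.35 SD at rho 0.3, 0.25 at 0.5, 0.15 at 0.7 and 0.05 at 0.9.

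**Planning.** The change variance is 2(1 - rho) and the residual variance is 1 - rho², a ratio of 2/(1 + rho). A later trial sized on the SD of change would be larger by 54%, 33%, 18% and 5% at rho 0.3, 0.5, 0.7 and 0.9 than one sized on the residual SD.

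**The case against.** The strongest reply is that the article does not exclude baseline adjustment. A linear model of change on arm and baseline also compares changes between groups. It gives exactly the same arm estimate and interval as a model of the post-programme value on arm and baseline, because subtracting baseline from the response only lowers the baseline coefficient by 1. The choice of covariates may sit in the pre-specified analysis plan. This stands: a reader might infer that the plan commits to an unadjusted analysis, but that would be an inference from silence. What remains is that the only method on the page is a comparison of mean changes, and someone following it literally would leave baseline out.

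Three further objections also stand.

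- **Validity.** A reader might infer that the change-score result is biased or its interval wrong. It is not. Over randomisations the difference is unbiased and coverage is nominal under the usual assumptions. The shift from imbalance is conditional on the allocation obtained and is already reflected in the interval: at rho 0.5, a shift of 0.25 SD compares with a half-width of 0.748 SD.
- **Scope.** A reader might extend the point to every non-feasibility outcome. The secondary outcomes serve to identify "cardiac risk factors such as hypertension, dyslipidemia, diabetes mellitus, obesity, and smoking status", and smoking status, for one, has no mean change.
- **Consequence.** The feasibility criteria (recruiting 40, 75% retention, all outcomes measured in 90%) do not depend on this choice. Nor does the article say that the SD of change will be carried forward; the paired data would yield the residual SD whichever comparison is reported.

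The reply that the gain is too small to matter stands only for high rho. It is trivial at 0.9 and slightly reversed at 0.95, but material at 0.3 to 0.5.

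**Conclusion.** The point holds for the continuous secondary and exploratory outcomes, as a matter of efficiency rather than error. The one between-group method stated is usually less precise than a baseline-adjusted comparison that needs no further data. The loss in interval width ranges from about 22% down to about 0.5% as rho goes from 0.3 to 0.9, and adjustment brings no gain near 0.95. Adjustment also removes the shift due to chance imbalance in the outcome's own baseline.

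The figures rest on equal SDs before and after, an equal split of completers and the 75% retention floor. At 20 per arm the width ratios are nearly the same, and the chance of an imbalance above 0.5 SD falls from about 17% to 11%. Because rho is unknown and probably differs between outcomes, no single figure for the loss can be given. The trial's feasibility conclusion does not depend on this.

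**What to change.** Add one sentence to Data assessment, or confirm that the analysis plan already contains it:

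> For each continuous outcome, the between-group difference will be estimated with its 95% confidence interval from a linear model of the post-programme value on arm and the baseline value of that outcome, with sex as a further covariate because it stratified the randomisation.

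Using the change as the response in the same model is equivalent. Keep the within-group mean changes as description, and report the residual SD of each model for planning the later trial. Categorical outcomes such as smoking status need their own summary and are not covered by this sentence.

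The cost is one degree of freedom per outcome for baseline and one more if sex is included. No new data are needed.
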